There have been multiple clinical trials and several systematic reviews reporting the application of SDF causing the arrest of caries lesions in a high percentage of cases (30–70%) [16,17,18,19,20,21,22,23,24]. Nearly 70% of caries lesions in primary teeth would be expected to be arrested in two years after SDF application with the variation of annual or biannual application as compared to combined controls of 5% NaF varnish or restorations. According to the AAPD manual [25], nearly 68% (95% CI = 9.7 to 97.7) of cavitated caries lesions in primary teeth would be expected to be arrested in two years after SDF application with a variety of annual or biannual application as compared combined controls of 5% Sodium fluoride (NAF) varnish or restorations. The American Dental Association (ADA) guidelines recommend the use of 38% SDF twice a year application over 5% NaF varnish (once per week for 3 weeks application) to arrest the cavitated caries coronal lesions in primary and permanent teeth [16]. However, it is a conditional recommendation that implies that not all patients would benefit from the intervention and depends on individual risk for caries, preferences, values, etc.

Studies are comparing various frequencies (thrice a year, weekly, biannual, annual, five times weekly per year, etc.) of SDF; however, the evidence is inconsistent. A clinical trial has shown that the yearly application of SDF has a higher proportion of arrested caries compared to the weekly application [26]. Biannual application of SDF was found to be superior compared to annual application in arresting cavitated carious lesion [27,28,29,30,31]. Annual application of silver diamine fluoride prevented many more carious lesions than application of fluoride varnish four times per year [26,31].

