## 2. Methods

### 2.1. Study Design

This trial is designed as a randomized, controlled trial consisting of three parallel arms with an allocation ratio of 1:1:1 (Figure 1).

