### 2.11. Sample Size

The sample size was calculated based on the primary objective. In an exploration study [26], those children treated weekly with 38% SDF had a slightly higher proportion of arrested caries compared to annual application. There was no considerable difference in the proportion of caries arresting by either semiannual or annual application (less than 10%). We expect that the proportion of the arrested carious lesion not to be more than 14% between the two frequencies of application. Considering a slightly higher proportion of caries arrest by the four times application as compared to others, we estimated the sample size at the power of 0.80 and alpha error of 0.05 to be 120 per arm. Being a population (tribal), which is not mainstream and owing to the demands of multiple follows of the tribal population, it is expected that we could encounter a lost-to-follow-up of about 30%. Accordingly, the final sample size has been increased to 160 children per arm. In total, 480 children will be enrolled on the trial.

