## 4. Statistical Methods

The outcome of the treated carious lesion is binary, either arrested lesion or failed to arrest at 6 months follow-up and at the end of 12 months follow up visit. The outcome will be assessed at two levels: Tooth-level—the proportion of cavitated surfaces at baseline will be compared with the proportion of the surfaces arrested at each frequency of application at 6 months follow-up and the end 12 months using chi-square methods. Between three frequencies of application (annual, semi-annual, and four times a year applications) the proportion of arrested surface at 6 months follow-up and end 12 months will be compared. This comparison will be stratified by type of tooth (posterior vs. anterior) and type of surfaces (facials vs. lingual). Child-level—each child may have one or more cavitated carious surface treated with SDF. So, the per-child proportion of cavitated carious lesions at baseline treated with 38% SDF applied at different frequencies that stayed arrested throughout observation will be determined.

The regression will be modelled on the dependent variable as a percentage of the arrested carious lesion per child with another. The two sets of analysis will be done, first, the intention-to-treat set, considering all patients as randomized regardless of whether they received the randomized treatment, and second, the “per protocol” analysis set. The hypothesis that four times application of 38% of SDF superior to other frequencies (annual or semi-annual application) is accepted, only if shown to be superior using both the “intention to treat” and “per protocol” analysis sets.

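### The superiority rule for the four-application arm does not say which visit, which analysis level or how many comparators decide it, so its error rate is not fixed at the stated 0.05

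*Protocol article*

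**What the plan says.** Section 4 (Statistical Methods) sets the condition for success: "The hypothesis that four times application of 38% of SDF superior to other frequencies (annual or semi-annual application) is accepted", but only when superiority appears in both the ITT and the per-protocol set.

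The results that could feed this rule are described just before it. The outcome is "either arrested lesion or failed to arrest at 6 months follow-up and at the end of 12 months follow up visit". At tooth level, the proportion of arrested surfaces is compared between the three frequencies at each of the two visits. At child level, there is one measure per child: the share of treated lesions that stayed arrested over the whole observation period. Section 2.8 assesses the primary outcome at both visits and ranks neither.

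The only error rate is in Section 2.11: "we estimated the sample size at the power of 0.80 and alpha error of 0.05 to be 120 per arm". The effect size there is a single contrast: "We expect that the proportion of the arrested carious lesion not to be more than 14% between the two frequencies of application".

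Section 5 gives a different rule for the analysis sets: one set is chosen by whether attrition is below 15%.

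**The concern.** An acceptance rule should point to the result that decides the trial. This one fixes the analysis-set condition and leaves three other things open: the visit, the level, and whether beating one comparator is enough. A reader holding a mix of significant and non-significant results could not tell whether the hypothesis had been accepted. Each open choice is also another chance of a false claim for the four-application arm.

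The open visit also affects what is being tested. In Table 1, the second application in Group 2 is given at the 6-month visit, when the outcome is also assessed. Up to that assessment, Groups 1 and 2 have had the same single baseline application, apart from anything applied that day. A 6-month win over the semi-annual arm would not test the semi-annual schedule, yet the rule does not exclude it.

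**Working it through.** **The plan's own figure.** Section 2.11 gives 120 per arm at power 0.80, alpha 0.05 and a difference of at most 14 points. It gives no base rate and no sidedness, so 120 has no unique derivation. The usual formula is

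n = [z(1−α/2)·√(2p̄q̄) + z(power)·√(p1q1 + p2q2)]² / (p2 − p1)².

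With p1 = 0.745, p2 = 0.885, p̄ = 0.815 and two-sided 0.05: (1.960 × 0.549 + 0.842 × 0.540)² / 0.0196 ≈ 119.6, so 120. One-sided 0.05 gives 121 at p1 = 0.67 and 118 at p1 = 0.68. The stated size is therefore compatible with one pairwise comparison at an undivided 0.05.

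**Counting the tests.** Two comparators × three results (surface level at 6 months, surface level at 12 months, child level over the whole observation) = 6.

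**Inputs to the error rate.**
- Correlation between the two comparisons: with "three parallel arms with an allocation ratio of 1:1:1" and equal variance v per arm mean, the shared arm gives v / (2v) = 0.5.
- Assumed: correlation between visits 0.5–0.8, between the child-level and each surface-level result 0.7–0.9, between ITT and per-protocol statistics 0.90–0.97.
- Assumed: each test at two-sided 0.05, counting only results in favour of arm 3 (z > 1.96), so the nominal rate is 2.5%.

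**Comparators alone.** With one visit and one level, P(z1 > 1.96 or z2 > 1.96) = 4.5% by simulation.

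**Six tests, correlated normal statistics.** In the first three result columns all arms are equal. In the last two, arm 3 truly beats one comparator, taken as a certain win, and equals the other, so the error is a false win on that second comparator.

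| Correlation: visits / levels | Any win, one set | Any win, both sets (0.90) | Any win, both sets (0.97) | Both comparators, both sets (0.90) | Both comparators, both sets (0.97) |
|---|---|---|---|---|---|
| 0.5 / 0.7 | 10.0% | 6.4% | 8.0% | 3.5% | 4.5% |
| 0.6 / 0.8 | 9.2% | 5.8% | 7.3% | 3.2% | 4.1% |
| 0.8 / 0.9 | 7.8% | 4.9% | 6.3% | 2.7% | 3.5% |

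The both-sets condition lowers the error by about 20% (8.0 against 10.0) to 37% (4.9 against 7.8), without bringing it to 2.5%. If Section 5 governs and only one set is analysed, the first result column applies, and the both-comparators case becomes 4.4–5.7%.

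**Sidedness.** If 0.05 is meant one-sided, the any-win error with both sets (0.90) is 9.8–12.5% against a nominal 5%.

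**The case against.** The strongest reply is that the protocol never says one win is enough. The wording is conditional (only if), and the bracketed annual or semi-annual may simply list what the other frequencies are, so that both must be beaten. Section 2.11 likewise speaks of four applications against the others. On that reading the comparators add no inflation. With all arms equal, the false-claim rate is then only about 0.6–1.1%, computed in a layout with more tests than the six used here. This stands as a legitimate reading. What remains is the open visit and level, which matter when one comparator is truly beaten and the other is not.

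The reply adds that no per-test level is stated, and that an alpha split or testing order could sit in an unseen analysis plan. That also stands: testing each result at 0.05 is an inference from the only alpha given. It does not remove the point, because the protocol itself states an acceptance rule and leaves out what decides it.

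A reader might infer something stronger: that any of eight tests wins at 0.05 each, so that the error is 20% or more and 0.05 is plainly not delivered. The documents do not support this. The child-level measure is one outcome over the whole observation, so there are about six tests. Two-sided counts include results against arm 3, and three-pair counts include arm 2 versus arm 1; neither can support the stated claim. The both-sets condition also has a real effect.

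**Conclusion.** The rule is underspecified in a way that affects the error rate. On the any-win reading, false superiority claims for arm 3 are about 8–10% against a nominal 2.5%, or about 5–7% when ITT and per-protocol must both win (8% at the highest correlation tried). On the both-comparators reading, the error is about 3–4.5% in the configuration where one comparator is truly beaten and the other is equal. The 0.5 correlation between comparisons follows from the allocation. The other correlations, the two-sided 0.05 per test and the normal approximation are assumptions. The finding is that the protocol does not fix the error rate and that plausible readings exceed the nominal level, not that any one of these figures is the trial's actual error.

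**What to change.** In Section 4:
- Name one deciding analysis, for example child-level arrest at 12 months, when the semi-annual schedule as defined in Section 2.7 has been given in full. Label the 6-month, surface-level and arm 2 versus arm 1 results secondary.
- State whether both comparators must be beaten. If so, test each at two-sided 0.05. If one suffices, test in a fixed order at two-sided 0.05, for example arm 3 versus arm 1 and, only if that succeeds, arm 3 versus arm 2. Name the comparator that each claim covers.
- Keep the both-sets condition or drop it explicitly, and reconcile it with Section 5, which selects one set by attrition.

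Cost: a few sentences and no added sample size. There would be no confirmatory claim from the secondary visit or level, and under the fixed order none on the second comparator unless the first step succeeds. Splitting alpha instead (0.025 per comparison) would hold the family-wise error at about 4.6%. It would, however, raise 120 per arm to 145 at 0.745 versus 0.885, or cut power at 120 from 0.80 to 0.71.

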Tribal children face many health disparities compared with the mainland counterparts [32]. The prevalence of ECC is 74.7% in these tribal children compared to their counterparts [7]. The oral health disparities for these children exemplify, many of the inequities and early care services in these communities. SDF as a chemotherapeutic agent for prevention and managing of ECC would be a crunch point as it is a simple technique, acceptable, and cost-effective strategy over restorations and hospital-based management. The SDF effectiveness in these high-risk caries children will generate the evidence to use SDF as a caries preventive tool to the population having less access to regular dental care. The trial findings may also help in reducing pain, improving quality of life, and significantly reducing costs, all contributing to substantial reductions in disparities in caries the disparities in between access to preventive care. The use of SDF to prevent or delay surgical intervention until after the age of 3 years makes it a potentially attractive adjunctive therapy for managing caries in the young pediatric population.

Though the evidence is clear that the use of 38% SDF is effective for arresting dental caries, the determination of an optimal SDF application frequency for a cavitated lesion in pragmatic settings is important especially among high caries risk tribal children who have poor access to oral care. Thus, the primary objective of this trial is to compare the effectiveness of an annual, semi-annual, and four times a year application of 38% Silver Diammine Fluoride in arresting active coronal carious lesions on primary teeth of tribal preschool children in India. The secondary objective is to assess the acceptability of SDF treatment by the child as well as parent/s.

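### The only acceptance rule pits four applications against annual or semi-annual without saying whether one or both must be beaten, and bi-annual versus annual has no decision rule

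*Protocol article*

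**What the plan says.** Section 1 of the Protocol article states that "the primary objective of this trial is to compare the effectiveness of an annual, semi-annual, and four times a year application" of 38% SDF. No arm is singled out. The abstract and the Introduction give the search for an optimal frequency as the reason for the trial.

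Section 4 plans a comparison of all three arms: "Between three frequencies of application (annual, semi-annual, and four times a year applications) the proportion of arrested surface at 6 months follow-up" and at 12 months is to be compared. No decision is attached to it. The only decision rule in the section is: "The hypothesis that four times application of 38% of SDF superior to other frequencies (annual or semi-annual application) is accepted, only if" it is "shown to be superior using both the “intention to treat” and “per protocol” analysis sets".

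Section 2.11 sizes the trial on a difference between two frequencies that it does not name: "We expect that the proportion of the arrested carious lesion not to be more than 14% between the two frequencies of application". It gives the expected direction as "Considering a slightly higher proportion of caries arrest by the four times application as compared to others".

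On bi-annual versus annual, section 1 reports that "Biannual application of SDF was found to be superior compared to annual application in arresting cavitated carious lesion". Section 2.11 reports "There was no considerable difference in the proportion of caries arresting by either semiannual or annual application (less than 10"%).

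**The concern.** The rule does not fit the objective in two ways.

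First, its *or* is unresolved. If superiority to either comparator suffices, four times can be declared superior to the other frequencies because it beats annual, even when it adds nothing over bi-annual. If superiority to both is needed, it cannot, except by chance. The two readings can give opposite conclusions from the same data, and the choice would be open after the results are known.

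Second, the rule can only speak for the four-times arm. If bi-annual is best and four times is no better than annual, the stated outcome is that the hypothesis is not accepted. The plan attaches no conclusion to the bi-annual advantage, and a reader may take the result to mean that frequency does not matter.

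The answer is meant to guide how often children with poor access to care must attend, so a claim for four times should name the arm that was beaten.

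**Working it through.** **Inputs.** Section 2.11 gives 160 enrolled per arm, about 30% loss, a 14-point difference, power 0.80 and alpha 0.05. Evaluable children: 160 × 0.70 = 112 per arm. The document gives no annual arrest rate, so 50% to 74.5% is assumed. Also assumed: one binary outcome per child, pooled pairwise z-tests at two-sided 0.05, and one analysis set.

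**1. The plan's own figure.** With p̄ the mean of the two rates and q = 1 − p,

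n = [1.96·√(2p̄q̄) + 0.8416·√(p₁q₁ + p₂q₂)]² / 0.14².

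- 74.5% vs 88.5%: (1.96 × 0.5491 + 0.8416 × 0.5401)² / 0.0196 = (1.0763 + 0.4546)² / 0.0196 = 119.6, so 120 per arm.
- 50% vs 64%: 196 per arm.

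The stated 120 can be neither confirmed nor refuted without a base rate. Two-sided and without continuity correction, it is matched near 74.5% vs 88.5% (or at the low-rate mirror). That sets the upper end of the range used here.

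**2. Bi-annual and four times equal, both 14 points above annual.** The chance that four times beats annual is about Φ{[0.14 − 1.96·√(2p̄q̄/112)] / √((p₁q₁ + p₂q₂)/112)}.

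- 50% vs 64%: (0.14 − 0.1297)/0.0655 ≈ 0.16, so about 0.56.
- 74.5% vs 88.5%: (0.14 − 0.1017)/0.0510 ≈ 0.75, so about 0.77.

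Simulation at 112 per arm (200,000 trials for the first row, 400,000 for the others):

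| Annual | Bi-annual = four times | Accepted, *either* | Accepted, *both* |
|---|---|---|---|
| 50% | 64% | 0.57 | at most 0.025 |
| 56% | 70% | 0.58 | 0.024 |
| 66% | 80% | 0.66 | 0.024 |
| 70% | 84% | 0.71 | 0.025 |
| 74.5% | 88.5% | 0.78 | 0.026 |

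At 120 per arm the *either* figure runs from 0.62 (annual 56%) to 0.81 (74.5%), and *both* stays near 0.025.

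**3. Bi-annual best.** With annual 50%, bi-annual 64%, four times 50% and 112 per arm, a three-arm chi-square test (2 df) is significant in 58% of trials. In 56% of all trials it is significant while four times beats neither comparator, so the acceptance rule has nothing to say about the difference found.

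**4. What requiring both costs.** If four times is truly 14 points above two equal comparators, 112 per arm gives *either* in 0.74 to 0.90 of trials and *both* in 0.42 to 0.66, for comparator rates of 56% to 74.5%.

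**5. Why a three-arm test first is enough.** With three arms, if any two of the pairwise equalities hold, all three arms are equal. The only intersection hypothesis is therefore the overall null. Testing it at 0.05, and then each pair at 0.05, is a closed procedure that holds the family error at 0.05. This would not carry over to four arms.

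**The case against.** - **The false credit depends on one reading.** The rule speaks of other frequencies in the plural, and section 2.11 compares four times with the others. Both fit *both* at least as well as *either*. This stands: a reader might infer that the plan will credit four applications wherever two do equally well, and the text does not support that without the condition. It does not settle the reading either, and that is the defect.
- **Bi-annual versus annual is not what shows whether two applications suffice.** This stands. Four times versus bi-annual shows that, and the rule names it, though only behind the *or*.
- **Bi-annual versus annual is not omitted from the analysis.** This stands. Section 4 compares all three arms and plans a child-level regression, so a bi-annual advantage would be estimated. Only the decision rule is missing. The sentence on the three frequencies also names no test; the chi-square in step 3 is an assumption.
- **The 57% to 78% is not a false-positive rate.** This stands. In that scenario four times really is better than annual. The fault is that the accepted statement is worded as superiority over the other frequencies. Requiring both analysis sets can only lower these figures.
- **Sections 1 and 2.11 seem to contradict each other on bi-annual versus annual.** This is tempting but weak. The statements rest on different cited studies, section 1 itself calls the evidence inconsistent, and superiority is compatible with a gap below 10 points.
- **Contrasts can be left to a statistical analysis plan.** This holds for detail. Here the protocol itself fixes an acceptance rule that does not match its objective.

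**Conclusion.** The point holds in a limited form. The objective is three-way, the single acceptance rule covers only four times, its *or* is unresolved, and bi-annual versus annual has no decision rule.

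The reading of *or* moves the chance of accepting four times from about 2.5% to between 57% and 78% when bi-annual does equally well. This assumes a 14-point gain over annual, 112 evaluable children per arm, one outcome per child, one analysis set, and annual rates of 50% to 74.5%. The base rate is an assumption; the gap between the readings is large across the whole range.

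If bi-annual is best and four times is no better than annual, both readings end in a bare non-acceptance, save for chance error. This should be settled before any comparative result is seen.

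**What to change.** In section 4, replace the acceptance sentence with the following.

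1. Three contrasts at 12 months: four times minus annual, four times minus bi-annual, and bi-annual minus annual, each reported as a risk difference with a 95% interval. Twelve months is the useful time point because Table 1 puts the second bi-annual application at the 6-month visit; up to then the annual and bi-annual arms have had the same treatment.
2. A three-arm test at 0.05 first and, only if it is significant, the three pairwise tests at 0.05.
3. Superiority of four times to the other frequencies is claimed only if it is superior to both. A win over one comparator is claimed against that comparator only.
4. A non-significant contrast is not evidence of equal effect.

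The existing requirement for both analysis sets can be carried over to each claim.

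Do not turn the 10% in section 2.11 into a similarity margin. It describes earlier results, and with equal rates the 95% half-width is 1.96·√(2p(1−p)/112), which is 0.120 at p = 0.3 or 0.7 and 0.131 at p = 0.5. No interval that wide can lie within 10 points either side of zero.

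Cost: wording only, with no added children or visits. Pairwise claims need a significant three-arm test first, and the *both* claim is harder to reach (step 4; the three-arm test can only lower those figures).

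### The stated power of 0.80 is for one two-frequency comparison; it is not the power of the acceptance rule, which needs both analysis sets and possibly both comparators

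*Protocol article*

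**What the plan says.** Section 2.11 of the protocol article bases the sample size on one contrast: "We expect that the proportion of the arrested carious lesion not to be more than 14% between the two frequencies of application". From this, "we estimated the sample size at the power of 0.80 and alpha error of 0.05 to be 120 per arm". The number is then raised to 160 per arm, 480 in total, for an expected loss of about 30%. The section names no analysis set, base arrest rate or sidedness, and mentions no second comparison.

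Section 4 names the comparators in its hypothesis: "The hypothesis that four times application of 38% of SDF superior to other frequencies (annual or semi-annual application". The same sentence then sets the condition for a positive conclusion, which is that this hypothesis "is accepted, only if shown to be superior using both the “intention to treat” and “per protocol” analysis sets". The section describes the ITT set as all patients as randomised.

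Section 5 gives a different rule for the sets: per-protocol analysis if attrition is under 15%, ITT otherwise. Under that rule only one set is analysed.

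**The concern.** The power figure and the decision rule are both printed, and they do not describe the same thing. The first belongs to one test of one difference. The second asks for success in two analysis sets and, if the other frequencies are meant jointly, against two comparators. The power of such a rule is at most that of its weakest component test, and equals it only if the other tests never fail when that one succeeds.

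At stake is how a negative result is read. If four-times application truly has the assumed advantage, it would be declared superior less often than the protocol promises. A reader who trusts the 0.80 could then take failure to accept the hypothesis as evidence that frequency does not matter, which is the trial's primary question.

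**Working it through.** **Inputs from the document.** Power 0.80, alpha 0.05, difference 14 points (worded as a maximum), 120 per arm before loss, 160 per arm enrolled, loss about 30%, semi-annual and annual differing by less than 10% (all Section 2.11); the acceptance rule (Section 4).

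**Assumptions.** Two-sided test; the child as unit with a binary outcome and no allowance for clustering of lesions; per-protocol set taken as the completers; the effect in non-completers varied.

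**The plan's own figure.** The 120 cannot be reproduced from the document alone, because no base rate is given. With n = [z(0.975)·√(2p̄q̄) + z(0.80)·√(p₁q₁ + p₂q₂)]² / 0.14², rates of 74.5% and 88.5% give (1.960 × 0.549 + 0.842 × 0.540)² / 0.0196, or 120. Rates of 68% and 82% give 149, with power 0.71 at 120. One-sided at 0.05, 68% against 82% gives 118. The 0.80 at 120 per arm is granted from here on.

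**Set-up.** Power 0.80 at 120 per arm means a noncentrality of 1.960 + 0.842 = 2.802. For n per arm it is 2.802·√(n/120). Two contrasts that share the four-times arm correlate at 0.5. A per-protocol set nested in ITT correlates with it at √(n_PP/n_ITT).

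**Set sizes.** ITT is 160 per arm. Per-protocol is 160 × 0.70 = 112 at the planned loss, or 120 if the pre-loss target is met.

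**One comparator, both sets required**

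| Per-protocol n | Correlation | Per-protocol alone | ITT alone, full effect | Both, full effect | ITT alone, half effect in non-completers | Both, half effect |
|---|---|---|---|---|---|---|
| 112 | √(112/160) = 0.837 | 0.77 | 0.90 | 0.76 | 0.79 | 0.71 |
| 120 | √(120/160) = 0.866 | 0.80 | 0.90 | 0.79 | 0.81 | 0.75 |

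With full effect, the ITT noncentrality is 2.802·√(160/120) = 3.235. With half effect in non-completers it is multiplied by (112 + 0.5 × 48)/160 = 0.85 or (120 + 0.5 × 40)/160 = 0.875. If non-completers carry no effect, power in both sets is 0.59 and 0.66. At 15% loss (136 completers) with full effect it is 0.83.

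**Both comparators required**

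- One set of 120, both gaps equal to the design difference: P(both succeed) with each at 0.80 and correlation 0.5 is 0.687. This figure does not depend on sidedness.
- Both sets, full effect: 0.63 with 112 completers, 0.67 with 120.
- One set of 120, gaps of 14 and 9 points (assuming semi-annual is 5 points better than annual, within the range in Section 2.11): the second noncentrality is 2.802 × 9/14 = 1.801, and joint power is 0.40.

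**Either comparator sufficient, in both sets, full effect, equal gaps.** 2 × (one comparator) − (both comparators) = 2 × 0.759 − 0.632 = 0.89 with 112 completers, and about 0.90 with 120.

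**The case against.** The strongest objection concerns size. A reader might infer that the rule has power of only about 0.54 to 0.74. Those figures follow if the ITT set is 120 per arm and per-protocol is 80% or 90% of it: 0.68 or 0.74 for one comparator in both sets, 0.54 or 0.60 for both comparators. The document does not support those denominators. The 120 is the number before inflation for loss, and ITT as randomised is 160. On the planned sizes with full effect in non-completers, the both-sets requirement costs only about 1 point beyond per-protocol power (0.80 to 0.79, or 0.77 to 0.76). At 112 completers, the other 3 points arise because 160 less 30% falls short of 120, which is a separate matter. A larger loss needs the assumption that non-completers benefit less. This objection stands and sets the size of the point.

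A reader might also infer that the wording requires four-times application to beat both other frequencies. It does not clearly do so, because annual and semi-annual are joined by *or*. On the either-one reading, power is not below 0.80 with full effect and equal gaps.

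Finally, Section 5 would run a single set, so the both-sets rule might never operate. That is a fair reason for not treating any one figure as settled. It does not rescue the 0.80, because Section 4 still states the acceptance rule explicitly.

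These objections leave the mismatch itself in place: the printed power is for one comparison, and nothing in Section 2.11 allows for the rule in Section 4.

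**Conclusion.** The point holds in a limited form: 0.80 is not the power of the written acceptance rule. For one comparator the shortfall at the planned loss is small, at 0.76 to 0.79 with full effect in non-completers and 0.71 to 0.75 with half; at 15% loss with full effect there is none (0.83). It is material if superiority over both frequencies is intended: about 0.69 in one set of 120, 0.63 to 0.67 in both sets, and about 0.40 in one set if the gaps are 14 and 9 points.

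All figures grant the plan its 0.80 at 120 per arm and the full 14 points, which Section 2.11 gives as an upper limit. They also rest on the assumed effect in non-completers and on taking per-protocol as the completers. The document fixes the direction for any rule that needs every test to succeed, but not the exact size.

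**What to change.** In Section 4:

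- Let the ITT comparison alone decide superiority, with per-protocol reported as supportive.
- Reconcile this with the Section 5 rule that runs only one set according to attrition.
- State whether the claim is superiority over both frequencies or over one named frequency. One workable order is four-times against annual first, then against semi-annual at 0.05 only if the first succeeds. If beating either one is enough, the claim must say so.

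In Section 2.11:

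- State that 0.80 applies to a single comparison.
- Print the lower power for superiority over both, about 0.69 at 120 evaluable per arm with equal gaps.
- If the both-sets rule is kept, replace 0.80 with the power computed for that rule under stated assumptions on set sizes and the effect in non-completers.

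The cost is a few sentences, a less favourable printed figure, and the loss of the per-protocol veto. Enrolment does not change.
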